**d) Sufficient time.**

**Explain the time that you and your research team will allocate to perform the research activities, including data analysis.**

Our goal enrollment is 120 patients. We anticipate that we will enroll 6 patients a month, so we estimate that we will enroll patients for 13 months and follow them for 3 months (Total 16 months).

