## 2. Study Procedures

**a) Please SUMMARIZE the research procedures, screening through closeout, which the research participant will undergo. Sections in the protocol attached in section 16 can be referenced, BUT do not copy the clinical protocol. Be clear on what is to be done for research and what is part of standard of care. For research involving collaborators, please specify the respective roles of Stanford and each collaborator on the protocol.**

Standard prehabilitation:

Patients will be provided with standard instructions in a hard-copy form specific to prehabilitation before surgery associating physical, nutritional, stress-reduction and cognitive recommendations without any personalized coaching for at least 3 weeks prior to surgery (see attached ControlGroup\_ProgramBook document).

Research Activities:

---

**Title :** Immune system modulation by enhanced vs standard prehabilitation program in patients undergoing elective major surgery - a prospective monocentric randomized single-blinded control . . .

**Approval Period:** 10/23/2023 - 12/31/2999

---

1. Screening: The research team will identify eligible patients by screening the clinic schedules of general surgeons.

2. Study Enrollment: Either in person during their surgical clinic visit, or by phone at least 28 days before surgery. If patients accept to be included, they will be randomized.

3. Baseline assessment (Day 0): Nutritional (using the Mediterranean Diet Scale), physical (by measuring 6 min walk test, Timed up and go, Five Times Sit to Stand Test and Wall Squat Tests), cognitive (using the qMCI test), anxiety (using the APAIS scale and the Pain Catastrophizing Scale) and quality of life status (using the SF36-scale) at baseline (prior to prehabilitation) will be recorded on RedCap by a personnel previously trained to the achievement of tests of the study.

4. Prehabilitation: SURGE or standard program will be proposed to the patients for 3-6 weeks.

SURGE consists in a 6-session (over 3-6 weeks) personalized prehabilitation program. This program will be delivered remotely with 2 in person (with a trained member of the research team) sessions every week. Self-exercises will be promoted every day.

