- > Adherence to prehab programs using a modified "Rehabilitation Adherence Measure for Athletic Training" scale
- > Physical status assessment including 6 Minute Walk Test (6MWT), Timed Up and Go (TUG), Five Times Sit to Stand Test & Wall Squat Test and Body Mass Index (BMI)
- > Prevalence and global severity of anxiety using questionnaires such as the APAIS (Amsterdam Preoperative Anxiety and Information Scale) and the Pain catastrophization scale.
- > Cognitive status evaluated by the qMCI

We will also evaluate the effect of prehab programs on post-operative outcomes by collecting:

- > Hospital length of stay
- > Readmission within 30 days after surgery
- > Postoperative complications scored by the Comprehensive Complication Index (CCI) within 90 days after surgery
- > Inpatient opioid use and pain levels during hospitalization
- > Neuropathic pain, quality of life and cognitive function assessed 30 days after surgery (in comparison to before surgery)

If the intervention is found to be clearly harmful then the study will be terminated before the total projected participant population has been enrolled. This will be determined by assessing for increase in complication rates after surgery beyond our baseline rates of complications (as determined by NSQIP data). These rates will be

**Title :** Immune system modulation by enhanced vs standard prehabilitation program in patients undergoing elective major surgery - a prospective monocentric randomized single-blinded control . . .

**Approval Period:** 10/23/2023 - 12/31/2999

calculated on a quarterly basis.

The study will end after complete enrollment (120 patients) or after 16 months of enrollment into the prehab intervention if no important differences are detected.

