**The risks of the Social well-being.**

There are no risks to the social well-being of the participants as the study protocol will not involve their social situation.

- b) **If you are conducting international research, describe the qualifications/preparations that enable you to both estimate and minimize risks to participants. Provide an explanation as to why the research must be completed at this location and complete the International Research Form. If not applicable, enter N/A.**

none

- c) **Describe the planned procedures for protecting against and minimizing all potential risks. Include the means for monitoring to detect hazards to the participant (and/or to a potential fetus if applicable). Include steps to minimize risks to the confidentiality of identifiable information.**

Administration of frequent surveys to detect increase in stress and pain levels will monitor for hazards. Also, patients will be closely monitored in the post-operative inpatient period for any physical problems.

The confidentiality of identifiable information will be protected as only the members of the study staff will

**Title :** Immune system modulation by enhanced vs standard prehabilitation program in patients undergoing elective major surgery - a prospective monocentric randomized single-blinded control . . .

**Approval Period:** 10/23/2023 - 12/31/2999

have access to the information, and the data will be stored on a secure computer (the PI's computer) which is password protected, encrypted by Stanford IT, and located in a locked office in a building under 24-hour surveillance.

- d) Explain the point at which the experiment will terminate. If appropriate, include the standards for the termination of the participation of the individual participant Also discuss plans for ensuring necessary medical or professional intervention in the event of adverse effects to the participants.**

The study poses only a small risk to participants. There is no plan to discontinue the study before all participants have been enrolled and samples have been collected. Drs. [name] and [name] will be available in the unlikely event that a participant needs medical attention as a result of study participation.

Individual participants may be terminated from the study if they choose to no longer be in the study.

In the event of adverse effects to the participants, the study staff will ensure that they receive the necessary medical and professional intervention.

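### The harm stopping rule judges complications against an NSQIP baseline, with no margin and without the randomised control arm, and section 9(d) contradicts it

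*Protocol*

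**What the plan says.** Section 2(g), Study Endpoint, commits to early termination for harm: "If the intervention is found to be clearly harmful then the study will be terminated before the total projected participant population has been enrolled". The next sentence says how harm will be established, namely by "assessing for increase in complication rates after surgery beyond our baseline rates of complications (as determined by NSQIP data", and adds that these rates will be "calculated on a quarterly basis". No baseline rate, margin, confidence bound or minimum number of patients is given. The rule does not say which complications count, over what period, or in which arm.

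A concurrent comparator exists. Section 2(a) says of eligible patients: "If patients accept to be included, they will be randomized". Section 2(g) also lists postoperative complications, scored to 90 days, among the outcomes collected.

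Section 9(d), on the point at which the experiment ends, says: "There is no plan to discontinue the study before all participants have been enrolled and samples have been collected".

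**The concern.** A harm rule has to separate harm caused by the programme from chance and from case mix. This one has three weaknesses as written.

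- **Comparator.** The baseline is outside the randomised comparison. Section 8(h) selects the trial population: it excludes ASA 4 or higher, palliative care, emergency or urgent surgery and expected stays under 48 hours, and it mixes several specialties. Nothing in section 2(g) says the baseline is restricted or adjusted to match. A gap between trial and baseline can therefore reflect selection.
- **No margin, repeated looks.** The only operational criterion is an increase beyond baseline, checked quarterly on small numbers.
- **Contradiction.** Section 2(g) provides for early termination and section 9(d) says none is planned. Both are current text.

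At stake is the only criterion the protocol gives for stopping the trial for harm. It could halt a harmless programme, or stay silent when SURGE patients do worse than controls.

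**Working it through.** The protocol states no error rate, threshold or baseline for this rule, so there is no figure to reproduce. What can be computed is how the literal rule behaves.

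**Inputs from the protocol**
- Target: "Our goal enrollment is 120 patients" (Resources, item d).
- Accrual: "we will enroll 6 patients a month, so we estimate that we will enroll patients for 13 months" (same item). Per quarter: 6 × 3 = 18.
- End of study: "The study will end after complete enrollment (120 patients) or after 16 months of enrollment into the prehab intervention" (section 2(g)).
- Number of quarterly looks: 13/3 gives about 4; 16/3 gives about 5; 120/6 = 20 months, and 20/3 gives about 7. The accrual figures do not agree with each other (6 × 13 = 78, not 120), so 4 to 7 looks are shown.

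**Assumptions**
- Allocation 1:1, so 18/2 = 9 SURGE patients per quarter.
- Baseline rate p0 between 10% and 40%.
- Outcomes known at each look.
- Literal trigger: cumulative events > p0 × cumulative patients at any look.

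**One look by hand.** With p0 = 20% and 9 patients, 9 × 0.20 = 1.8, so 2 events cross the line. If the true rate is also 20%, P(X ≥ 2) = 1 − 0.8^9 − 9 × 0.2 × 0.8^8 = 1 − 0.134 − 0.302 = 0.564.

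**All looks, no harm (true rate = p0).** Exact binomial recursion on cumulative counts, discarding at each look the paths that have already crossed. Chance of at least one crossing, SURGE arm:

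| p0 | 4 looks | 5 looks | 6 looks | 7 looks |
|---|---|---|---|---|
| 10% | 0.77 | 0.79 | 0.80 | 0.81 |
| 15% | 0.66 | 0.71 | 0.72 | 0.74 |
| 20% | 0.72 | 0.74 | 0.78 | 0.79 |
| 25% | 0.67 | 0.70 | 0.73 | 0.76 |
| 30% | 0.73 | 0.75 | 0.77 | 0.79 |
| 40% | 0.72 | 0.74 | 0.77 | 0.78 |

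The range is 66% to 81%. Seven full quarters give 63 SURGE patients; capping the arm at 60 gives 73% to 80% in the last column. Judging each quarter alone is worse: 87% or more throughout.

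**True rate below baseline, no harm.** With p0 = 30% and true rate 15%, the chance of any crossing is about 16% at 4 to 7 looks.

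**Harm against control, trial population below baseline.** Assume baseline 30%, control 15%, SURGE 25%. No crossing at any look: about 45% of trials on the SURGE rate (47% at 4 looks, 44% at 7), and about 82% if both arms are pooled.

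**Changing only the comparator.** SURGE against control with no margin, 7 looks, 60 per arm: any excess still stops about 72% of harmless trials (rates 20% or 30%). A threshold is needed as well.

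**The case against.** The strongest reply is that the governing words require the programme to be *clearly* harmful, so a one-event excess was never meant to end the trial. This has force. If *clearly* meant, say, a one-sided exact p below 0.025 against baseline at each look, false triggering would be about 5%. A numerical boundary could also sit in a monitoring document not shown. A reader might infer that this trial would probably be stopped without cause. The protocol does not support that: the 66% to 81% describes the literal rule with a true rate equal to baseline. What remains is that the sentence defining the qualifier supplies only an increase over baseline. A later document could add a number but could not change the comparator without contradicting section 2(g).

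Second, false alarms and missed harm need different assumptions: the first is worst when the trial rate equals the baseline, the second when it lies well below. That is correct, and the two should not be added together. The direction of selection is also unknown: excluding ASA 4 or higher lowers risk, while excluding short stays raises it. The baseline might be procedure-specific; the text does not say.

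Third, a reader might judge sensitivity by the final cumulative rate alone, where the 25% SURGE arm exceeds the 30% baseline in only about 15% of trials. That is not the rule. Rates are checked quarterly, and on that footing the excess is flagged in about 55% of trials.

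Fourth, outcomes will lag, since surgery is at least 28 days after enrolment and complications run to 90 days. The figures are therefore approximate. Finally, the protocol describes the intervention as minimal risk, which bears on urgency but not on whether the rule works.

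**Conclusion.** The point holds. Section 2(g) fixes an external comparator, attaches no margin to a quarterly check, does not name the arm and leaves the randomised control unused; section 9(d) contradicts it. The contradiction and the choice of comparator rest on the text alone. The sizes rest on the literal reading, 1:1 allocation, prompt outcomes and assumed baseline rates.

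Under those conditions the error rate depends mainly on where the unstated baseline lies relative to the trial population, which the rule does not control. When the rule does fire, the crossing is not evidence of harm against control. This should be fixed. It is not fatal to the trial, because the qualifier leaves room for judgement and the protocol rates the intervention as low risk.

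**What to change.** In section 2(g), define the harm criterion as the cumulative complication rate in SURGE against concurrent control, for named complications in a fixed post-operative window. State an evidence threshold, and have it trigger a formal review. Keep the NSQIP rates as context. Reconcile sections 2(g) and 9(d) so that they say the same thing about early termination.

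One illustration of a threshold: from the second quarterly look, review if the posterior probability that the SURGE rate exceeds control is above 0.98, with flat priors (each arm's posterior is Beta(events + 1, non-events + 1)). By simulation with 9 per arm per quarter:
- false triggers: about 3% to 6% at rates of 20% to 30% (4 to 7 looks);
- 30% v 50%: detected in about 62% of trials at 6 looks;
- 15% v 25%: detected in only about 19% to 34% (4 to 7 looks).

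The last figure is below the 55% or so at which the literal rule fires when the baseline is 30%. The proposal therefore buys a controlled false-trigger rate and a valid comparison, not more sensitivity to modest harm. That limit comes from the sample size and should be stated in the protocol.

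The cost is one paragraph in section 2(g) and one sentence in section 9(d), using outcomes already collected. Whoever runs the check will see counts by arm, so it should be someone who neither coaches nor assesses participants.

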**Identify exclusion criteria.**

Children ( $<18$  years), patients undergoing emergency or urgent surgery  
Patients undergoing surgery in  $<28$  days, non-english speakers will not be included. Premorbid conditions or orthopedic impairments that contraindicated physical exercise, cognitive disabilities, ASA score 4 or higher or patient under palliative care, expected length of stay at hospital  $< 48$  hours and no access to internet will be also criteria of non inclusion.

**i) Describe your screening procedures, including how qualifying laboratory values will be obtained. If you are collecting personal health information prior to enrollment (e.g., telephone screening), please request a waiver of authorization for recruitment (in section 15).**

Screening will be performed by the PD who will screen the electronic medical records of the patients to be seen in the clinics of the colorectal surgeons to identify potential participants. A waiver of authorization for recruitment will be requested.

**j) Describe how you will be cognizant of other protocols in which participants might be enrolled. Please explain if participants will be enrolled in more than one study.**

We will ask the patients if they are in any other protocols (except the protocol IRB #46978 in which they could be included). They will be allowed to be enrolled in other studies as long as they do not interfere with this study (for example, they may be enrolled in Tissue Bank or GenePool, but not in any other rehabilitation, diet, or exercise studies).

**k) Payment/reimbursement. Explain the amount and schedule of payment or reimbursement, if any, that will be paid for participation in the study. Substantiate that proposed payments are reasonable and commensurate with the expected contributions of participants and that they do not constitute undue pressure on participants to volunteer for the research study. Include provisions for prorating payment. See payment considerations**

There will be no monetary compensation for the study.

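### The protocol's statements on study end and duration contradict each other, and none gives every patient time to complete the 90-day post-operative complication index

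*Protocol*

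**What the plan says.** Four places in the protocol bear on when the study ends or how long it lasts.

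- Section 2g (Study Endpoint): "The study will end after complete enrollment (120 patients) or after 16 months of enrollment into the prehab intervention if no important differences are detected". Both triggers are enrolment events, and no follow-up is added.
- Resources, d) Sufficient time: "Our goal enrollment is 120 patients", "We anticipate that we will enroll 6 patients a month", and "we estimate that we will enroll patients for 13 months and follow them for 3 months (Total 16 months").
- Section 8m: 90 days of active participation per patient, and 6 months as the probable length of the whole study.
- Section 9d: no plan to stop before enrolment and sample collection are complete. Outcome follow-up is not mentioned.

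The time each patient needs is fixed elsewhere. Section 2a, step 2, places telephone enrolment "by phone at least 28 days before surgery", and the exclusion criteria in section 8h rule out "Patients undergoing surgery in $<28$ days". Step 4 of section 2a gives a programme of 3 to 6 weeks in both arms. Among the post-operative outcomes in section 2g is "Postoperative complications scored by the Comprehensive Complication Index (CCI) within 90 days after surgery". Readmission, neuropathic pain, quality of life and cognition are taken to 30 days after surgery.

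**The concern.** The end of the study is tied to enrolment, while the post-operative outcomes are timed from surgery, which comes at least four weeks after enrolment. The 16 months is the enrolment period in section 2g and the entire study in the Resources section. Section 8m's 6 months is shorter than either enrolment period. A team following section 2g would close with recent patients still inside their outcome windows. A team following the Resources section would close later, but still too early for the last patients.

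The CCI accumulates complications over its window. A patient cut off before day 90 is scored too low if analysed as observed, and is lost to that outcome if dropped.

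**Working it through.** **Inputs.** From the protocol: target 120 and 6 patients a month (Resources, d); 13 months of enrolment plus 3 of follow-up (same place); 16 months of enrolment (section 2g); at least 28 days from enrolment to surgery (sections 2a and 8h); windows of 30 and 90 days after surgery (section 2g). Assumptions: uniform accrual, no dropout, and surgery 28 to 42 days after enrolment. The 42 days is a six-week programme begun at enrolment and followed directly by surgery. A month is 30.44 days.

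**The plan's own figures.** The sum 13 + 3 = 16 months reproduces. The accrual does not: 6 × 13 = 78 and 6 × 16 = 96, while 120 / 6 = 20 months. The enrolment period is therefore itself uncertain, and more than one length is shown below.

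**Time needed per patient, from enrolment.**
- To day 90: 28 + 90 = 118 days (3.88 months), or 42 + 90 = 132 days (4.34 months).
- To day 30: 28 + 30 = 58 days, or 42 + 30 = 72 days.

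**Per-patient figure in section 8m.** If the 90 days run from enrolment, they end at post-operative day 90 − 28 = 62 at the latest, and at day 90 − 42 = 48 with a six-week wait.

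**Share of patients unable to reach an endpoint** = max(0, time needed − follow-up after last enrolment) / enrolment duration.

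| Reading | Enrolment | Follow-up after last enrolment | Short of day 90 | Short of day 30 |
|---|---|---|---|---|
| Resources, d) | 13 months (395.7 d) | 3 months (91.3 d) | (118 − 91.3)/395.7 = 6.7% to (132 − 91.3)/395.7 = 10.3% | none (58 and 72 are below 91.3) |
| Section 2g, at 120 patients | 20 months (608.8 d) | 0 | 118/608.8 = 19.4% to 132/608.8 = 21.7% | 58/608.8 = 9.5% to 72/608.8 = 11.8% |
| Section 2g, at 16 months | 16 months (487.0 d) | 0 | 118/487.0 = 24.2% to 132/487.0 = 27.1% | 58/487.0 = 11.9% to 72/487.0 = 14.8% |

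Under the Resources plan the shortfall for the last patient is 118 − 91.3 = 27 days to 132 − 91.3 = 41 days. That affects about 8 to 12 patients if 120 are enrolled in 13 months. Under section 2g, at 6 a month, 23 to 26 patients fall short of day 90 at either trigger, out of 120 or of 96.

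If the 3 months of follow-up were kept but enrolment took longer, the day-90 share would be 5.5-8.4% for 16 months and 4.4-6.7% for 20 months.

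**The case against.** The strongest reply is that the section 2g sentence answers a form question about early termination and about when the study stops if no difference emerges. It says the study ends after enrolment, not at that moment, and nothing says that data collection stops for patients already enrolled. The Resources section does plan follow-up, so section 2g is not the only statement on study end. This stands in part. It makes the Resources plan the fairer guide to intent, and the smaller figures of 7-10% belong beside the larger ones. It does not remove the problem, because that plan is itself 27 to 41 days short and the durations still disagree.

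Three stronger readings are tempting, and the documents do not support them.

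- A reader might infer that up to a third of patients are cut off. That figure (118/395.7 = 29.8% to 132/395.7 = 33.4%) needs 13 months of enrolment with no follow-up. The 13 months appears only together with 3 months of follow-up, so no stated scenario combines the two.
- A reader might infer a bias between arms, because the standard programme is described in one place as lasting at least three weeks. Step 4 of section 2a gives both arms 3 to 6 weeks, and nothing lets the arm determine the date of surgery.
- A reader might object that no rule covers patients with incomplete windows. That is commonly left to the statistical analysis plan, which is not at hand.

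It is also fair to say that the stated purpose concerns immune cells, with adherence and before-and-after measures alongside. None of these needs day 90.

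**Conclusion.** The point holds as an internal contradiction with a real but limited consequence. The study-end statements cannot all be followed, and none covers the 118 days or more that each patient needs. About 7-10% of patients miss day 90 under the Resources plan, and about 19-27% under section 2g read literally. Day-30 outcomes are safe under the former and missed by about 10-15% under the latter. These shares rest on uniform accrual and a wait of 28 to 42 days. The 28 days is the protocol's minimum, and a longer wait for surgery raises every day-90 figure. The CCI is one of several additional post-operative outcomes and is not named as primary, so the severity is moderate to minor. The point is separate from the accrual arithmetic: with feasible accrual the end date would still be too early.

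**What to change.** In section 2g, state that enrolment closes at 120 patients, that any calendar cap applies to enrolment only, and that the study ends, with the final analysis of post-operative outcomes, when the last randomised patient has reached 90 days after surgery.

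In Resources, d), restate follow-up after the last enrolment as the wait for surgery plus 90 days: at least 118 days, in practice about 4 to 4.5 months. Give a matching total. At the minimum wait this is 13 + 3.9 = 16.9 months, 16 + 3.9 = 19.9 months or 20 + 3.9 = 23.9 months, depending on the enrolment period adopted. Bring section 8m's 90 days and 6 months into line.

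The cost is a wording change in three places and about 1 to 1.5 months of calendar time beyond the 3 months of follow-up already planned. No patients or visits are added.

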These research procedures pose minimal risk to the patient, as the exercises are tailored for patients' baseline level of fitness, nutritional, cognitive and anxiety status to reduce the risk of injury. Moreover prehabilitation has been demonstrated to be safe and beneficial to surgical outcomes.

**c) State if deception will be used. If so, provide the rationale and describe debriefing procedures. Since you will not be fully informing the participant in your consent process and form, complete an alteration of consent (in section 13). Submit a debriefing script (in section 16).**

**Title :** Immune system modulation by enhanced vs standard prehabilitation program in patients undergoing elective major surgery - a prospective monocentric randomized single-blinded control . . .

**Approval Period:** 10/23/2023 - 12/31/2999

Deception will not be used.

- d) State if photo, audio or video recording will occur. Describe what will become of the photos or recording after use, e.g., shown at scientific meetings, erased. Describe the final disposition of the recordings.**

Audio/video recording will not occur.

- e) Describe alternative procedures or courses of treatment, if any, that might be advantageous to the participant. Describe potential risks and benefits associated with these. Any standard treatment that is being withheld must be disclosed in the consent process and form. (i.e. standard-of-care drug, different interventional procedure, no procedure or treatment, palliative care, other research studies).**

There are no proven alternative procedures for Prehab. Standard treatment is not being withheld.

- f) Will it be possible to continue the more (most) appropriate therapy for the participant(s) after the conclusion of the study?**

Patients may choose to continue any/all of the prehab program components as long as they wish.

- g) Study Endpoint. What are the guidelines or end points by which you can evaluate the different treatments (i.e. study drug, device, procedure) during the study? If one proves to be clearly more effective than another (or others) during the course of a study, will the study be terminated before the projected total participant population has been enrolled? When will the study end if no important differences are detected?**

The endpoints we will use to evaluate the adherence to prehab programs (compared to one arm to the other) will compare before and after prehab program time and are:

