**l) Costs. Please explain any costs that will be charged to the participant.**

There will be no costs that will be charged to the participants.

**m) Estimate the probable duration of the entire study. Also estimate the total time per participant for: (i) screening of participant; (ii) active participation in study; (iii) analysis of participant data.**

Probable duration of the entire study: 6 months

Per participant:

(i) screening: 15 minutes

(ii) active participation in study: 90 days

(iii) analysis of data: 1 hour

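### As worded, the 16-month end of study depends on undefined between-arm differences, would take effect before 120 patients are enrolled, and conflicts with the protocol's other timelines

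*Protocol*

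**What the plan says.** Four places in the protocol bear on when the study ends.

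- **Section 2, g) Study Endpoint.** The rule is that the study ends when 120 patients are enrolled or "after 16 months of enrollment into the prehab intervention if no important differences are detected". It answers a form item that asks "When will the study end if no important differences are detected". The same section lists adherence, physical, anxiety and cognitive measures and a set of postoperative outcomes. It marks none as the one that decides whether a difference is important. A separate harm rule compares complication rates with a baseline every quarter.
- **Resources, d) Sufficient time.** "Our goal enrollment is 120 patients"; "We anticipate that we will enroll 6 patients a month"; and "we estimate that we will enroll patients for 13 months and follow them for 3 months (Total 16 months").
- **Section 8, m).** "Probable duration of the entire study: 6 months".
- **Section 9, d).** "There is no plan to discontinue the study before all participants have been enrolled and samples have been collected".

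**The concern.** A condition on observed differences, attached to the end of enrolment, is a stopping rule. This one does not say which outcome counts, how large a difference is important, who looks, or what boundary applies. If it is applied as written, someone has to compare the arms at 16 months and decide from the result whether to recruit further. The final size then depends on the data through an open criterion. Power changes, and the estimate from a trial that went on because a difference was seen is biased away from zero.

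This would be minor if the target were reached well before 16 months. At the planned accrual it is not. The same figure of 16 months also means enrolment in one section and total duration in another, so the protocol does not fix when the clause would apply.

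**Working it through.** **1. The plan's own timeline.** The inputs from Resources, d) are a target of 120, 6 patients a month, 13 months of enrolment and 3 months of follow-up.

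- The sum 13 + 3 = 16 months is correct.
- Enrolment needed: 120 / 6 = 20 months. The stated 13 months is not reproduced.
- Enrolled in 13 months: 13 × 6 = 78 (65% of 120, 42 short).
- Enrolled in 16 months: 16 × 6 = 96 (80% of 120, 24 short).
- Rate needed for 120: 120 / 13 = 9.2 a month, or 120 / 16 = 7.5 a month.
- With the plan's own 3 months of follow-up, 120 patients at 6 a month take about 20 + 3 = 23 months.

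The 16-month clause is therefore reached before the target.

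**2. The statements side by side.**

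| Place | What it fixes |
|---|---|
| Section 2, g) | 16 months of enrolment, conditional on no important differences |
| Resources, d) | 16 months in total, of which 13 are enrolment |
| Section 8, m) | 6 months for the whole study (6 × 6 = 36 patients at the stated rate) |
| Section 9, d) | no planned discontinuation before full enrolment |

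No two of these agree. Section 9, d) also conflicts with the harm stop in Section 2, g).

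**3. What the conditional rule would do (illustration).** The protocol gives no alpha, power, effect size or SD. Assume 1:1 allocation, one continuous endpoint, a two-sided 5% test and 80% power at 120. Assume also that all enrolled patients have outcomes at the look and that important means p<0.05.

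- Detectable standardised difference at 120: (1.960 + 0.842) × √(2/60) = 0.51. The expected Z at 120 is 2.80.
- Fixed stop at 96: expected Z is 2.80 × √0.8 = 2.51, so power is Φ(2.51 − 1.96), about 71%.
- Fixed stop at 78: the same formula with √0.65 gives about 62%.
- End at 96 if p>0.05, otherwise retest at 120: success needs significance at both looks. Simulation of bivariate normal statistics with correlation √0.8 (4 million draws) gives 68.5% power and 2.9% type I error.
- Bias among trials that continue: the mean of Z at 96, given Z>1.96, exceeds its expectation by φ(0.55)/Φ(0.55), about 0.49. Carried to 120 this is 0.49 × √0.8, about 0.43. Relative to 2.80 that is an overestimate of about 16%.
- If significance at either look could be claimed, type I error would be 7.1% (same simulation).

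Of the fall from 80% to about 69%, about 9 points come from having 96 patients instead of 120. Only about 2 points come from the condition.

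**The case against.** The strongest counter-argument is that no interim look was intended. The conditional words repeat the form's question, the protocol describes no between-arm efficacy analysis during the study, and the only scheduled monitoring is the quarterly complication check. On that reading the sentence is a calendar cap. This is plausible and cannot be excluded. But the answer keeps the condition, so the text does not say so, and the accrual shortfall and the conflicts remain under that reading.

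A reader might go further in three ways that the document does not support.

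- **That unblinded results will be reviewed.** Detecting a difference between arms would need results by arm, but the protocol never says that anyone will look at them. This is an inference from the literal wording.
- **That type I error is inflated.** The sentence ends the study when no difference is seen, which acts like a futility rule and lowers the error rate to 2.9% in the illustration. The 7.1% needs an early difference to be claimable, which the protocol does not say.
- **That the many listed measures give a large familywise error from this rule.** That is multiplicity at the end of the trial, a separate matter commonly left to the analysis plan.

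It is also fair to object that most of the power loss is due to accrual, and that a fixed date set at 16 months would keep it. That stands, so the fix has to deal with the accrual figure as well as the condition. An analysis plan could define a boundary, but it would not remove the conflicts within the protocol.

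**Conclusion.** The point holds as a defect of wording and timeline. The end-of-study sentence in Section 2, g), taken literally, lets between-arm results decide the final size with nothing defined. At the stated accrual it would operate at 96 patients, or at 78 if 13 months of enrolment is meant. The accrual arithmetic (20 months needed, not 13) and the conflicts among the four sections do not depend on what the authors intended.

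The size of the statistical effect does depend on assumptions. Under those in the working, power is about 69% with the conditional rule, against about 71% with a fixed stop at 96 and 80% at 120. Type I error is 2.9%, and trials that continue overestimate the effect by about 16%. These figures assume that all 96 patients have outcomes at the look. For the 90-day complication index that cannot be so, because surgery is at least 28 days after enrolment.

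**What to change.** In Section 2, g), state that enrolment ends at 120 randomised patients or at a fixed calendar date, whichever comes first, regardless of observed between-arm differences, and that no between-arm efficacy comparison is made before then. Keep harm monitoring as a separate rule.

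Correct the enrolment period in Resources, d) to match the accrual rate: 20 months for 120 patients at 6 a month, or restate the number expected by the chosen date (96 for 16 months of enrolment, 78 for 13). Then reconcile Section 2, g), Resources, d), Section 8, m) and Section 9, d), including the tension between the last of these and the harm stop.

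The cost is protocol wording. The informal option to stop early for lack of effect is lost, and either the stated duration becomes longer or the expected size becomes smaller.
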